**Fig. 2 Fig2:**
[figure not shown]
Study flowchart. Abbreviations: bmGT = bis(methylthio)gliotoxin; BALF = bronchoalveolar lavage fluid; GM = galactomannan; IPA = invasive pulmonary aspergillosis; LFD = lateral flow device; RT-PCR = real time polymerase chain reaction; TAFC = triacetylfusarinine

### Sputum induction and sample processing

Sputum induction using hypertonic saline (4.5%) and spirometry (KoKo PD Instrumentation, Louisville, KY) will be performed as previously described [38]. 4.5% saline will be inhaled from an ultrasonic nebulizer for doubling time periods (from 30 s to 4 mins), and a fixed cumulative sputum induction time of 15 min will be used for all participants.

Fungal culture will be performed on 100 μL of sputum plugs carefully separated from saliva and inoculated directly onto potato dextrose agar [39]. The plates will be sealed and incubated for 7 days at 37 °C. After 7 days, *Aspergillus* will be identified based on macroscopic and microscopic features.

A minimum volume of 0.5 mL of sputum plugs will be pipetted into a sterile falcon centrifuge tube, and 8 volumes of phosphate buffer solution will be added, vortexed and incubated at room temperature for 30 mins, and 1.5 mL of the above sputum suspension will be stored for *A*-DNA extraction and RT-PCR assay.

A total of 200 μL of filtered suspension will be used for quality assessment as previously described [38]. Briefly, in an adequate number of cells, the presence of pulmonary macrophages and the proportion of squamous cells are examined. A total cell count of leukocytes and cell viability is performed, and samples with a squamous cell percentage greater than 50% or viability less than 40% are excluded. The remainder of the sample will go through a sterile filter (Merk Millipore Ltd., Ireland) and will be stored in aliquots at − 80 °C for subsequent GM, LFD, TAFC and bmGT detection.

### BALF collection and sampling

Fibreoptic bronchoscopy with bronchoalveolar lavage is performed in accordance with the American Thoracic Society guidelines [40]. Briefly, the bronchoscope will be placed in a wedge position within the selected bronchopulmonary segment. A total volume of 40 mL of normal saline (at room temperature) will be divided into two aliquots and instilled through the bronchoscope. After the instillation of each aliquot, instilled saline will be retrieved with a negative suction pressure of less than 100 mmHg that can avoid visible airway collapse. The retrieved BALF (at least 5 mL) will be subdivided into aliquots within 1 h of collection after being shaken to ensure homogeneous mixing, and stored at − 80 °C for GM detection.

### GM detection

Peripheral venous blood will be collected into Vacutainer® tubes (BD Worldwide, Suzhou, China), and serum will be obtained by centrifugation at 3000 rpm, 4 °C for 10 mins. The GM assay on serum, BALF and sputum will be performed with the Platelia *Aspergillus* enzyme immunoassay (Bio-Rad, California, USA) according to the manufacturer’s instructions. Tests for serum and BALF GM will be considered positive at cut-off values of ≥0.5 ODI and ≥ 1.0 ODI, respectively.

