### LFD performance

LFD will be performed as Thornton et al. described [36]. Briefly, 100 μL pretreated serum (1:1 diluted with tissue culture medium), neat BALF or processed sputum supernatant will be added to the release port on the LFD device after gentle mixing and will be incubated at room temperature for 15 mins. The development of the control line in the result window shows that the test has run correctly, and the development of the *Aspergillus*-specific test line will be determined after 15 mins. The results will be recorded as positive if the test line is present, or be recorded as negative if the test line is absent. Each LFD result will be assessed by two researchers independently.

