### Statistical analysis

The data will be analysed with SPSS 22.0 software (IBM Corp, Armonk, NY, USA). Two analyses will be performed based on the IPA classification, one in which patients with possible IPA will be excluded in the calculation and a second analysis in which patients with possible IPA will be classified as not having IPA. Therefore, the comparisons and analyses will be (1) proven/probable IPA versus no IPA, and (2) proven/probable IPA versus possible/no IPA [43]. The sensitivity, specificity, negative predictive value (NPV), positive predictive value (PPV), and diagnostic odds ratio, including 95% confidence intervals, will be calculated for different biomarkers. ROC analysis will be performed and AUC (including 95% CI) and cut-off values will be established from the ROC curves for GM, RT-PCR, TAFC and bmGT. The McNemar χ^2^ test will be used to compare sensitivity, specificity, NPV, and PPV between different assays. The difference in hospital stay and the survival between possible or no IPA versus proven or probable IPA will be analysed with chi-square tests, and the relationships between the levels of biomarkers and the hospital stay and survival will be analysed via regression models. *P* < 0.05 will be defined as statistically significant.

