Potential diagnostic biomarkers for IPA have been intensively studied, given the problem of an early diagnosis. We have reviewed the literature systematically to identify potential biomarkers that can be detected in a sputum sample. Galactomannan (GM) is a cell wall polysaccharide that is released by *Aspergillus* during fungal growth. The method of GM detection has been commercialized and widely used in the clinic with serum and BALF samples [19]. The serum GM assay exhibits low sensitivity (23.1–42%) for the diagnosis of IPA in non-haematological patients [6, 23], whereas BALF GM shows higher sensitivity and specificity [6–9]. The GM assay for sputum samples has been established in several studies (Table 1). Whether a GM assay based on lower airway derived sputum can be used as a non-invasive tool for the diagnosis of IPA deserves investigation. The measurement of GM in sputum might provide a more sensitive and non-invasive diagnostic approach for IPA.

GM detection can be affected by non-*Aspergillus* fungi and food that contains GM and beta-lactam antibiotics, which can produce false-positive values [49–51]. Several other biomarkers have been shown to play a role in the diagnosis of IPA and may be potential candidates for future clinical use. A rapid detection with LFD is an immunochromatographic assay that uses a monoclonal antibody called JF5 that targets an extracellular glycoprotein secreted during active fungal growth [36]. The test can be performed bedside and accomplished within 15 mins and, therefore, can be used as an early indicator for *Aspergillus* infection. The device is highly specific to antigens from *Aspergillus* but does not react with antigens from a large number of clinically important fungi, especially *Candida species* [36]. Pan et al. [52] conducted a meta-analysis to investigate its diagnostic accuracy for invasive aspergillosis, and showed that the LFD assay using BALF had higher sensitivity (86%) and specificity (93%) than serum (68% sensitivity and 87% specificity). Importantly, the BALF LFD assay also exhibited satisfying diagnostic performance for IPA (77% sensitivity and 92% specificity) in patients with URD [11]. Sputum supernatant has a similar matrix as BALF after processing procedures; hence, the use of the sputum LFD assay may provide a bedside and time-saving diagnostic tool for IPA.

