There are concerns about the specificity of the sputum assay related to colonization or contamination. Nevertheless, the four biomarkers (GM, JF5 antigen, TAFC, bmGT) in our study are produced and released during fungal growth. It is less likely that the increase in the levels of these biomarkers is a result of contamination of fungal spores. In addition, lower airway secretions will be used by sputum induction, and sputum quality control by squamous cell counting and viability calculation will further exclude the possibility of contamination. We will also determine an appropriate cut-off value of different sputum biomarkers, which will help to differentiate colonization from infection.

There are several highlights of this study. We systematically evaluate the validity of various biomarkers based on sputum from lower airways for the diagnosis of IPA for the first time; in particular, the establishment of a method that simultaneously detects TAFC and bmGT in sputum is first described and applied for patents and reported. Furthermore, the study population, i.e., patients with URD, has been increasingly recognized to present with IPA, which is associated with high mortality [12], but only has been addressed in a small number of studies. We assess the sputum biomarkers for IPA diagnosis in this population for the first time, and the results may help to provide novel, non-invasive and valuable diagnostic tools for IPA in patients with URD. In addition to sputum, serum and BALF will also be collected and compared for their diagnostic performance. In the statistical analysis, we will conduct two different analyses to investigate the impact of the possible IPA group on the interpretation of the results. Except for the investigation of diagnostic efficacy, we will also conduct a clinical follow-up to observe the prognosis of different types of IPA and further investigate host factors predisposing to IPA in patients with URD.

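### Sputum GM is cut at a threshold taken from this sample and serum GM at a fixed one, so the planned McNemar test on sensitivity partly compares thresholds rather than specimens

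*Protocol article*

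**What the plan says.** The same GM immunoassay is run on serum, BALF and sputum. Positivity is fixed in advance for two of the three specimens: "Tests for serum and BALF GM will be considered positive at cut-off values of" 0.5 ODI for serum and 1.0 ODI for BALF (GM detection). No value is set for sputum. The Background cites 1.2 ODI from an earlier study in haematological patients, but the protocol does not adopt it.

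The Statistical analysis section says that "cut-off values will be established from the ROC curves for GM, RT-PCR, TAFC and bmGT". It does not name the specimen, but the Discussion does: "We will also determine an appropriate cut-off value of different sputum biomarkers".

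LFD has a fixed visual rule in every specimen: "The results will be recorded as positive if the test line is present" (LFD performance).

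The McNemar "test will be used to compare sensitivity, specificity, NPV, and PPV between different assays" (Statistical analysis), and the Discussion adds that "serum and BALF will also be collected and compared for their diagnostic performance". AUCs with 95% confidence intervals are to be reported, but no test of a difference between AUCs is named.

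**The concern.** Sensitivity can be compared between two tests only if their specificity is comparable too. The Discussion says "The serum GM assay exhibits low sensitivity" in non-haematological patients, giving 23.1 to 42%, and describes serum assays as highly specific. A threshold that serves serum in that way lies well towards the specific end of its ROC curve. A cut-off read from the sputum ROC curve may lie much nearer the middle. McNemar on sensitivity would then mainly detect where the two thresholds sit. The Discussion raises the possibility that sputum GM is the more sensitive approach, and this test could appear to confirm it even if the two specimens discriminated equally well.

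A second, smaller effect is that a cut-off chosen and evaluated on the same patients looks better than it is, while a fixed rule gets no such benefit.

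**Working it through.** **The plan's own figure.** Sample size calculation: a = 1.414 × Φ⁻¹(0.795) = 1.165; V = 0.0099 × exp(−a²/2) × (6a² + 16) = 0.1213; n = 1.96² × 0.1213 / 0.09² = 57.5, so 58 per group. The stated 59 is close enough, and 59 + 59 is used below.

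**Inputs from the protocol.** AUC 0.795 and 59 per group (Sample size calculation); serum GM sensitivity 23.1 to 42% (Discussion).

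**Assumptions not in the protocol.** Sputum and serum GM share one equal-variance binormal ROC curve with AUC 0.795; the sputum cut-off maximises Youden's J in the sample; the correlation between assays is 0.3 to 0.7; McNemar is exact, two-sided, at 0.05.

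**Serum operating point.** The shift between cases and controls is μ = √2 × Φ⁻¹(0.795) = 1.165. A fixed cut-off c with sensitivity s satisfies c = μ − Φ⁻¹(s), and its specificity is Φ(c).
- s = 23.1%: c = 1.165 + 0.736 = 1.901, specificity 97%
- s = 42%: c = 1.165 + 0.202 = 1.367, specificity 91%
- s = 60%: c = 1.165 − 0.253 = 0.912, specificity 82%
- serum at its own optimum: c = μ/2 = 0.583, sensitivity and specificity both 72%

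**Sputum operating point.** Over simulated trials the in-sample Youden cut-off shows about 76% sensitivity and 73% specificity. The same cut-offs in new patients give about 72% and 70%.

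**Apparent result when the two assays discriminate equally:**

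| Serum sensitivity / specificity | Sputum gain in sensitivity | McNemar significant for sputum | Sputum loss in specificity |
|---|---|---|---|
| 23.1% / 97% | about 51 to 53 points | over 99% of trials | about 22 to 24 points, significant in about 86 to 91% |
| 42% / 91% | about 31 to 34 points | roughly 88 to 95% | about 17 to 18 points, significant in about 60 to 70% |
| 60% / 82% | about 16 points | about 50 to 58% | about 9 points (82 − 73) |
| 72% / 72% (own optimum) | about 4 points | about 16 to 21% | none on average |

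The gains follow from the operating points, for example 76 − 42 = 34. The spread from 31 to 34 reflects how ties at the maximum of J are broken. Taking the highest tied cut-off gives the lower figure, and would also reduce the last two rows.

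**Benchmark.** With both assays cut in advance at the same specificity, sensitivities are equal (45.4% each at 90% specificity) and McNemar rejects in about 2.5 to 3% of trials.

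**Tuning alone.** With the comparator fixed at its true optimum, mean J is 0.496 for the tuned assay and 0.442 for the fixed one, a difference of 0.054. In new patients the tuned cut-off gives J of about 0.422. Most of the gap in the first two rows is therefore a difference in operating point, not optimism.

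**The case against.** **The fixed cut-offs serve another purpose.** A positive serum or BALF GM is a mycological criterion in Table 2, so those thresholds are needed to classify patients. The Statistical analysis section names no specimen for its GM cut-offs, so ROC cut-offs for serum and BALF are not excluded. This stands as an ambiguity. The positivity rule for serum and BALF is nevertheless fixed, the Discussion ties the derived cut-offs to sputum, and the article itself states both rules and the test that joins them.

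**The operating points are assumed.** No criterion is given for the sputum GM cut-off, and the Discussion wants it to separate colonization from infection, which could lead to a more specific choice. No numerical serum GM specificity is given either; the 91% and 97% are model results. This stands, and is why the size is given as a range.

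**The trade-off would be visible.** Specificity, PPV and NPV are tested too, and the AUC does not depend on a cut-off. This also stands. A reader might infer that a finding of sputum superiority is close to guaranteed. The documents do not support that: the distortion concerns sensitivity read alone, and the same analysis would usually show sputum losing specificity. What the plan lacks is a contrast that resolves the two opposing results.

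**BALF and LFD differ.** A reader might extend the serum argument to BALF GM. The Discussion and Table 5 describe BALF as both sensitive and specific, so a low-sensitivity operating point is not supported there. LFD follows the same fixed rule in sputum, so for it too only in-sample tuning of its rivals is at issue.

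**Incorporation works the other way.** Serum and BALF GM help define probable IPA, which favours them and may offset part of the effect. It is a separate bias of unknown size and does not make the comparison sound.

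**Some of this could sit in an unseen analysis plan.** That is true of optimism correction as such. The unequal threshold rules and the McNemar comparison are in the article.

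**Conclusion.** The point holds for sputum against serum GM. As written, a significant McNemar result on sensitivity would not show that sputum discriminates better. With identical ROC curves and the cited 42% serum sensitivity, sputum would look about 31 to 34 points more sensitive, significant in roughly 88 to 95% of trials, and about 17 points less specific, significant in about 60 to 70%. At 60% serum sensitivity the gain is about 16 points; with serum at its own optimum it is about 4. These figures rest on the equal-variance binormal model, a shared AUC of 0.795, a Youden cut-off and the assumed correlations, none of which the protocol fixes for this comparison. For BALF GM and LFD the supported effect is in-sample tuning only, about 0.054 in J.

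**What to change.** 1. Make a paired AUC difference (DeLong or bootstrap) the main contrast for sputum against serum GM and sputum against BALF GM.
2. As a secondary analysis, set the sputum GM cut-off to the comparator's specificity in the no-IPA controls and compare sensitivities there, with a bootstrap that re-derives the cut-off in each resample. Restrict this to proven/probable versus no IPA. In the second planned analysis possible IPA counts as non-diseased, yet by Table 3 those patients lack mycological criteria and so cannot be positive on serum or BALF GM; matching to that inflated specificity would penalise sputum.
3. When ROC-derived sputum cut-offs are compared with LFD, report bootstrap- or cross-validation-corrected accuracy.
4. State that no conclusion of sputum superiority over serum will rest on McNemar for sensitivity alone.

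The data are already to be collected, so the change is to analysis wording. The cost is precision and a smaller apparent sputum advantage. In these scenarios the matched sensitivity difference has a standard deviation of about 12 to 14 points. At 97% comparator specificity, 0.971^59 ≈ 18% of trials would have no false positive among 59 controls, so the sputum cut-off would then rest on the single highest control value. That is why the matched comparison should stay secondary. None of this removes the advantage serum and BALF GM gain from being part of the reference standard.

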### LFD performance

LFD will be performed as Thornton et al. described [36]. Briefly, 100 μL pretreated serum (1:1 diluted with tissue culture medium), neat BALF or processed sputum supernatant will be added to the release port on the LFD device after gentle mixing and will be incubated at room temperature for 15 mins. The development of the control line in the result window shows that the test has run correctly, and the development of the *Aspergillus*-specific test line will be determined after 15 mins. The results will be recorded as positive if the test line is present, or be recorded as negative if the test line is absent. Each LFD result will be assessed by two researchers independently.

### *A*-DNA extraction and RT-PCR

Fungal DNA will be extracted from 1.5 mL of the sputum suspension with the commercial MycXtra fungal DNA extraction kit (Myconostica Limited, Manchester, UK), and *A*-DNA will be detected with the MycAssay *Aspergillus* kit (Myconostica Limited, Manchester, UK), according to the manufacturer’s instructions. PCR runs will be performed on a CFX Connect™ RT-PCR system (Bio-Rad, California, USA) by targeting a portion of the 18S ribosomal gene, in accordance with the detection kit protocol. Ten microliters of extracted DNA will be used in a final reaction volume of 25 μL. The PCR protocol is as follows: 10 mins at 94 °C; 10 s at 94 °C, 58 s at 57 °C, and 20 s at 72 °C for 40 cycles. The cycling threshold will be recorded and used for subsequent analysis, including the determination of an optimal cut-off value, based on which the sputum samples will be regarded as positive or negative for *Aspergillus* infection.

### TAFC and bmGT detection

High-performance liquid chromatography tandem mass spectrometry (HPLC-MS/MS) on Agilent 1260–6460 (Agilent Technologies Inc., Santa Clara, USA) was first developed in our laboratory and will be used to simultaneously analyse TAFC and bmGT from sputum. The method employs phenacetin as the internal standard, and shows the lower and upper limits of quantitation for TAFC and bmGT assays of 1.56 ng/mL and 100 ng/mL, respectively. Upon detection, 100 μL of sputum will be spiked with phenacetin, vortexed and extracted with 400 μL of dichloromethane. The extraction process will be repeated once, and the total solvent will be evaporated with a pressure gas blowing concentrator. The residue will then be reconstituted in 100 μL of acetonitrile/water (50/50 *v*/v%), vortexed and centrifuged. Three microliters of supernatant will be injected for HPLC-MS/MS analysis. Standards of TAFC (EMC, Germany) and bmGT (Enzo Life Sciences, Inc., USA) are spiked into sputum samples from four patients with bacterial pneumonia to evaluate the recovery of both compounds. Each of the four sputum samples is divided into three aliquots, with one aliquot as a control and the other two spiked with different concentrations of TAFC and bmGT. We assayed one sputum sample from a patient diagnosed with lung cancer (squamous cell carcinoma) and probable IPA using the HPLC-MS/MS method.

### Clinical follow-up

Patients will receive telephone reviews at 3 months and 6 months after enrolment. Information that includes the patients’ symptoms, days of hospitalization and survival will be recorded and checked in the medical record system.

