**Discussion:**

We have developed and verified the feasibility of *Aspergillus*-related biomarker assays for sputum. The study findings will contribute to a novel look at the diagnostic performance of sputum biomarkers in IPA and provide important insight into the improvement of the early diagnosis of IPA, particularly in patients with URD.

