### Diagnostic criteria

The diagnostic criteria of IPA are based on the 2008 EORTC/MSG framework [17]. Host factors, clinical criteria and mycological criteria to establish the diagnosis of IPA in this study population are listed in Table 2. In accordance with the study by Prattes et al. [11], URD is added as one of the host factors. We propose to make this modification due to several reasons. Host factors of the diagnostic criteria in previous guidelines were originally defined for haematological patients but have not been validated in non-neutropenic patients. Additionally, those typical host factors promoted by EORTC/MSG are frequently absent in non-haematological patients [2, 23]. Patients will be classified into proven, probable, possible and no IPA groups according to the revised 2008 EORTC/MSG criteria [17] (Table 3).

**Table 2 Tab2:** The diagnostic framework for IPA in patients with URD

Host factors	Recent history of neutropenia (< 0.5 × 10^9^ neutrophils/L for > 10 days) temporally related to the onset of infection Prolonged use of corticosteroids at a mean minimum dose of 0.3 mg/kg/day of prednisone equivalent for > 3 weeks Treatment with immunosuppressants during the past 90 days Inherited severe immunodeficiency Underlying respiratory diseases including chronic pulmonary diseases (COPD, asthma, lung cancer, bronchiectasis, interstitial lung diseases, and cystic fibrosis) and acute pulmonary diseases (bacterial pneumonia, viral pneumonia, and acute bronchitis)
Clinical criteria	The presence of 1 of the following 3 signs on chest computed tomography: Dense, well circumscribed lesion(s) with or without a halo sign Air-crescent sign Cavity on chest computed tomography
Mycological criteria	Cytologic or microscopic evidence of *Aspergillus* elements or recovery of *Aspergillus* in sputum or BALF Positive GM test in serum or BALF

**Table 3 Tab3:** IPA classification according to revised 2008 EORTC/MSG criteria

Proven IPA	Histopathological or cytopathological examination of lung tissue showing *Aspergillus* hyphae from needle aspiration or biopsy specimen with evidence of associated tissue damage, OR positive culture result for *Aspergillus* from a sample obtained by sterile procedure from the lung.
Probable IPA	Host factors, AND clinical criteria, AND mycological criteria
Possible IPA	Host factors AND clinical criteria
No IPA	Other cases excluded from proven, probable and possible IPA groups

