### Participants screening and recruitment

The study flowchart is shown in Fig. 2. Patients with respiratory diseases admitted into the hospital will be screened for inclusion and exclusion criteria for recruitment. The recruited patients will be subsequently assessed according to the clinical criteria shown in Table 2, namely newly-developed abnormalities in CT scan associated with IPA, for the classification of no IPA or suspected IPA groups. Patients without clinical criteria will be identified as no IPA. For patients with typical clinical criteria, those presenting histopathological or cytopathological evidence of *Aspergillus* hyphae from needle aspiration or biopsy specimen, or positive culture result for *Aspergillus* from a sample obtained by sterile procedure from the lung will be identified as proven IPA. If lung biopsy is not performed or negative result is generated, mycological examinations will be performed including sputum/BALF culture or serum/BALF GM tests to further classify patients as probable or possible IPA. Sample collection and testing will be required to be performed prior to antifungal treatment.

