This study has some limitations that should be considered. The categories of probable and possible IPA are proposed for immunocompromised patients only in the consensus report by the EORTC/MSG. However, this report recognizes that the revised definition of IPA does not necessarily apply to immunocompetent patients as it is difficult to find a sufficient basis for identifying appropriate host factors. Patients with URD may possess much different risk factors to *Aspergillus* infection compared to those immunocompromised individuals. As in the study by Prattes et al. [11], pre-existing respiratory disease is added as an independent host factor to establish the diagnosis in our study. We will also conduct post hoc analyses of the host factors linked to diagnosis and prognosis for further investigation. The concentration of biomarkers in the sputum may fluctuate with the production and expectoration of the sputum and the releasing of the biomarkers from the infection site. However, this study already includes a great number of biomarkers from different sample types with a comparable large sample size, and we do not perform serial tests for sputum biomarkers at different time points across the disease course, which may lead to the underestimation of the diagnostic performance of several biomarkers. Further study may be warranted to investigate the dynamic variation of different *Aspergillus* biomarkers in sputum.

In conclusion, the design and protocol of a clinical trial that investigates the performance of sputum signatures for the diagnosis and prognosis of IPA in patients with URD are presented here. The results of this innovative study are expected to provide answers to the following questions. Are sputum signatures valuable diagnostic tools for IPA in patients with URD? Which signature is the strongest potential candidate? Would the modified host factors be appropriate for this patient population? What disease course of IPA would present in this population? The study findings will provide evidence and novel insights into these areas, which have not been accessed.

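### Controls are defined by the absence of CT signs and follow-up is not used to verify them, so early IPA not yet visible on CT counts against a positive sputum marker

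*Protocol article*

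**What the plan says.** **Aim.** The Abstract (Discussion paragraph) expects the findings to "provide important insight into the improvement of the early diagnosis of IPA, particularly in patients with URD". The Background and the main Discussion also give early diagnosis as the motivation.

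**Classification.** Under Participants screening and recruitment, recruited patients are assessed on the clinical criteria, "namely newly-developed abnormalities in CT scan associated with IPA, for the classification of no IPA or suspected IPA groups". Table 2 defines those criteria as "The presence of 1 of the following 3 signs on chest computed tomography". The rule for the rest is: "Patients without clinical criteria will be identified as no IPA". Biopsy and mycology are described as the next step only for patients who have the signs. No date is given for the CT, and no repeat CT is mentioned.

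**Analysis.** The Statistical analysis section makes two comparisons. Patients with no IPA are on the non-diseased side in both. Patients with possible IPA join them in the second.

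**Follow-up.** The Clinical follow-up section states: "Patients will receive telephone reviews at 3 months and 6 months after enrolment". Besides symptoms, "days of hospitalization and survival will be recorded and checked in the medical record system". The Discussion gives the purpose: "we will also conduct a clinical follow-up to observe the prognosis of different types of IPA". The Statistical analysis section analyses hospital stay and survival, and does not use follow-up to revise IPA status.

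**Limitations.** The Discussion concedes that "we do not perform serial tests for sputum biomarkers at different time points across the disease course". It links this to fluctuating marker levels, not to the timing of the reference standard.

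**The concern.** Underlying respiratory disease is both an inclusion criterion and a host factor, so every participant meets the host criterion. In the sequence described, the CT signs alone then separate no IPA from the other groups. A patient sampled before lesions are visible is a control, and a positive sputum result in that patient is an error of the marker, even if IPA is diagnosed within the following months.

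Such a patient is one whom an early test is meant to find. The article itself says that the radiological features of IPA are atypical and that this hinders early diagnosis, yet it uses the absence of typical radiological signs to define the controls. At stake are apparent specificity, the AUC, and any statement about early diagnosis. As described, the analysis measures accuracy against status at presentation and has no means of showing whether a positive marker came before CT-visible disease.

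**Working it through.** **1. The plan's own figure.** Sample size calculation section: AUC 0.795, d = 0.09, two-sided α = 0.05.
- a = 1.414 × φ⁻¹(0.795) = 1.165
- V = 0.0099 × exp(−a²/2) × (6a² + 16) = 0.1213
- n = 1.96² × 0.1213 / 0.09² = 57.5, so 58 per group against the stated 59

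This reproduces closely and does not bear on the point. The stated 59 controls are used below.

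**2. Specificity.** Let f be the share of controls who have early IPA at sampling, Sp the true specificity, and Se the marker's sensitivity in those early cases. At a fixed cut-off:

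Apparent specificity = (1 − f) × Sp + f × (1 − Se)

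Loss = f × (Sp + Se − 1)

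The loss is positive for any marker with Sp + Se above 1. With Se = 100% it reaches its maximum, f × Sp.

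The article gives no value for f, so f is assumed. The Background reports a specificity of 62.2% for sputum GM in a haematology study; 90% is an assumed upper illustration.

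| Converters among 59 | f | Loss at Sp 62.2% | Loss at Sp 90% |
|---|---|---|---|
| 3 | 3/59 = 5.1% | 0.622 × 3/59 = 3.2 points | 0.90 × 3/59 = 4.6 points |
| 6 | 6/59 = 10.2% | 0.622 × 6/59 = 6.3 points | 0.90 × 6/59 = 9.2 points |

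If only 70% of the early cases are marker-positive, the losses are smaller. At f = 5% and 10% they are 1.6 and 3.2 points for Sp 62.2%, and 3.0 and 6.0 points for Sp 90%.

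**3. AUC.** If the misclassified controls have the same marker distribution as the cases, each comparison of a case with such a control has probability 0.5:

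Apparent AUC = (1 − f) × 0.795 + f × 0.5
- f = 5%: 0.95 × 0.795 + 0.05 × 0.5 = 0.780
- f = 10%: 0.90 × 0.795 + 0.10 × 0.5 = 0.766

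The shift is about 0.015 or 0.03, against a planned margin of error of 0.09.

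**The case against.** The strongest reply is that this argues from silence in a condensed article. The follow-up list is worded as examples, and the full protocol may include re-adjudication. That is fair, and it limits the finding to what the article describes. But the point does not rest on silence alone: the article states the control rule, states both comparisons, and gives follow-up a prognostic purpose.

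A second reply is that the working objective in the Background is diagnostic performance in this population, with early diagnosis as the hoped-for contribution. Accuracy at presentation does answer that objective. This is why the two planned analyses can stay, and why rewording the conclusion is an acceptable alternative. A third is that the AUC shift is well inside the planned margin. That is true, but the margin describes random error, whereas this is a bias that a larger sample does not remove.

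Some stronger readings are tempting but not supported:
- **That cases enter only once CT signs and mycology are present.** The inclusion criteria require neither, and classification follows recruitment.
- **That status is stated to be fixed at an enrolment CT.** No CT date or closing time for classification is given.
- **That a possible patient confirmed a few days later stays non-IPA.** Sputum culture runs for 7 days and feeds the split between probable and possible, so later mycology already counts.
- **That TAFC or other early-rising markers lose most.** The article says TAFC is secreted early, but also that GM, the JF5 antigen, TAFC and bmGT are all released during fungal growth. It does not rank markers by lead time.
- **That each converter costs a full 1/59 of specificity.** This holds only at a true specificity of 100%.

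**Conclusion.** The concern holds in a limited form. Under the stated rules, a marker-positive control with early IPA not yet visible on CT is a false positive in both analyses, and the article describes no use of follow-up to find such patients. For an informative marker the bias in specificity and AUC is downward.

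Its size is unknown, because the article gives no conversion rate. The illustrated losses of 3.2 to 9.2 points of specificity assume 3 to 6 converters among 59 controls, all marker-positive. The AUC figures also assume case-like marker levels before any CT sign. With few converters, or weaker marker signal before CT signs, the effect is small. The limit on claims about early diagnosis does not depend on these figures.

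**What to change.** **Record.** At the medical-record check already planned under Clinical follow-up, add three dated items for patients classed as no or possible IPA: any later proven or probable IPA, the first typical CT sign, and the first positive mycology. Later status should be judged without knowledge of the sputum biomarker results. No extra CT or sampling is asked for.

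**Analyse.** In the Statistical analysis section, keep the two planned comparisons unchanged and add one sensitivity analysis. It removes from the controls those no or possible IPA patients who reach proven or probable IPA by 3 months. List these patients with their enrolment marker results and the interval from sampling to diagnosis.

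**Word.** If this is not done, describe the conclusion as diagnosis at presentation, not early diagnosis.

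**Cost.** Three data items, a blinded judgement of the few patients concerned, and one extra analysis. The sample size is unaffected. There are two drawbacks. Some later IPA will be newly acquired, not missed at sampling, which is why the interval must be shown. Later CT and mycology will also be done selectively, so converters will be found incompletely.
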